## Abstract

**Introduction:**

Preterm birth complications are the most common cause of death in children under 5 years. The presence of multiple microorganisms and genital tract inflammation could be the common mechanism driving early onset of labour. South Africa has high levels of preterm birth, genital tract infections and HIV infection among pregnant women. We plan to investigate associations between the presence of multiple lower genital tract microorganisms in pregnancy and gestational age at birth.

**Methods and analysis:**

This cohort study enrols around 600 pregnant women at one public healthcare facility in East London, South Africa. Eligible women are ≥18 years and at <27 weeks of gestation, confirmed by ultrasound. At enrolment and 30–34 weeks of pregnancy, participants receive on-site tests for *Chlamydia trachomatis* and *Neisseria gonorrhoeae*, with treatment if test results are positive. At these visits, additional vaginal specimens are taken for: PCR detection and quantification of *Trichomonas vaginalis*, *Candida* spp., *Mycoplasma genitalium, M. hominis*, *Ureaplasma urealyticum* and *U. parvum*; microscopy and Nugent scoring; and for 16S ribosomal RNA gene sequencing and quantification. Pregnancy outcomes are collected from a postnatal visit and birth registers. The primary outcome is gestational age at birth. Statistical analyses will explore associations between specific microorganisms and gestational age at birth. To explore the association with the quantity of microorganisms, we will construct an index of microorganism load and use mixed-effects regression models and classification and regression tree analysis to examine which combinations of microorganisms contribute to earlier gestational age at birth.

**Ethics and dissemination:**

This protocol has approvals from the University of Cape Town Research Ethics Committee and the Canton of Bern Ethics Committee. Results from this study will be uploaded to preprint servers, submitted to open access peer-reviewed journals and presented at regional and international conferences.

**Trial registration number:**

NCT06131749; Pre-results.

STRENGTHS AND LIMITATIONS OF THIS STUDYThis cohort study takes a holistic approach, investigating both the presence and quantity of multiple lower genital tract microorganisms, including vaginal microbiota, in pregnancy and their associations with gestational age at birth.The study is set in a location where the prevalence of genital tract infections and adverse pregnancy outcomes is high, uses ultrasound scans to assess gestational age at enrolment accurately, and uses state-of-the-art molecular diagnostic methods.The study setting is limited to one research site, which may affect the generalisability of the findings.The use of gestational age at birth as a continuous outcome, instead of preterm birth as a dichotomous outcome, might limit comparability with other studies, but we will also examine the binary outcome preterm birth in secondary analyses.

## Introduction

Preterm birth complications are the most common cause of death in children under 5 years.^1^ Close to 1 million infants die every year because they are born preterm (before 37 completed weeks of gestation), mainly from infectious, respiratory and neurological complications, and those that survive can experience long-term morbidity.^1 2^ South Africa has a high incidence of preterm birth at around 10%,^3^ around 30% of women have one or more curable sexually transmitted infections during pregnancy^4 5^ and about 30% of pregnant women are living with HIV.^6^

Microbial colonisation or infection during pregnancy, in the lower or upper genital tract, has been reported to predispose to preterm birth, as do anatomical, biochemical, endocrinological, immunological, nutritional, environmental and psychosocial factors.^7 8^ The presence of microorganisms may contribute to early onset of labour directly, through presumed ascension from the lower to the upper genital tract, or indirectly, through a pathway of inflammatory response, or a combination of both.^7 9^ Inflammation may be the common pathway, even if infection has not reached the amniotic cavity.^10^

Much of the research reporting on the role of sexually transmitted infections in pregnancy and preterm birth has focused on single infections, such as *Chlamydia trachomatis,*^11^
*Neisseria gonorrhoeae*^12^ and *Trichomonas vaginalis*.^13^
*Mycoplasma genitalium* is the most recently recognised bacterial sexually transmitted infection and, while an association with preterm birth has been reported, there are few studies with prospective data collection.^14^ Bacterial vaginosis is the most common vaginal microbiota dysbiosis and is associated with adverse pregnancy outcomes, either alone or in combination with other sexually transmitted infections.^15–17^ Associations with adverse birth outcomes have also been observed for other genital mycoplasmas, *M. hominis, Ureaplasma urealyticum* and *U. parvum*.^18^ For individual sexually transmitted infections, bacterial vaginosis and colonisation by other genital mycoplasmas, summary ORs for the association with adverse birth outcomes in meta-analyses of univariable data are generally around 1.3–2.0.^11–14 16 18^
*Candida* spp have not been found to be associated with preterm birth, but an association with more inflammatory, symptomatic yeast infection cannot be ruled out.^19^ Most studies about these microorganisms do not present analyses that examine the role of co-occurrence or control for confounding factors, so the presence or strength of the causal association cannot be assessed.^20^ It is also important to include women living with HIV, among whom there are fewer studies about associations between genital tract infections and adverse birth outcomes than among women without HIV infection.^21 22^

The importance of the quantity of different microorganisms as a driver of preterm birth has not been extensively studied,^23–25^ but might be as, or more, relevant than their presence.^23^ Together with inflammation or immune activation in the genital tract during pregnancy, organism load could be an important driver of the early onset of labour and preterm birth.^8 23 24 26 27^ This calls for a holistic approach to research studies, which combines information about the presence of different microorganisms, the quantified load and the microbiome, sociodemographic factors and HIV among women living with infection, most of whom are receiving antiretroviral therapy. The overall aim of this study is to investigate associations between the presence of lower genital tract microorganisms in pregnancy and preterm birth and other adverse pregnancy outcomes. This will be achieved through three objectives to explore: (1) the association between the presence of specific lower genital tract microorganisms and gestational age at birth (primary outcome), as well as secondary adverse pregnancy outcomes; (2) the association between quantified load of vaginal and sexually transmitted microorganisms and gestational age at birth (primary outcome) as well as secondary adverse pregnancy outcomes; and (3) the combinations of microorganisms that are most strongly associated with earlier gestational age at birth.

## Methods and analysis

### Study design and setting

This prospective closed cohort study follows women enrolled during pregnancy until after they give birth (figure 1). The study is conducted at the antenatal clinic of one primary healthcare facility in Buffalo City Metropolitan Municipality, Eastern Cape Province, South Africa. This cohort study is part of a larger project, called Philani Ndiphile (meaning ‘be healthy and I will be healthy’ in isiXhosa), which includes a randomised implementation-effectiveness trial of screening strategies for sexually transmitted infections in pregnancy^28^ and a case–control study about persistent *C. trachomatis* infection.

**Figure 1 F1:**
[figure not shown]
Study visits and specimen collection. CT, *Chlamydia trachomatis*; NG, *Neisseria gonorrhoeae*.

### Participants

Inclusion criteria: Pregnant women aged 18 years or older, who live in Buffalo City Metropolitan Municipality, intend to deliver in the same municipality and provide written informed consent to take part in the study. The eligible gestational age at enrolment, confirmed by ultrasound, was below 20 weeks at the start of the study in March 2021 and was increased to 27 weeks in September 2021 to increase enrolment and to align with another trial.^29^

Exclusion criteria: Participation in any other research study or inability to understand and speak a local language (English, Afrikaans or isiXhosa).

### Enrolment

A trained study field worker approaches all pregnant women attending an antenatal care visit at the clinic and individually informs them about the study. If a potential participant shows interest in the study, the study field worker checks for eligibility. The date of the last menstrual period is used initially to estimate gestational age. If all eligibility criteria are met, a study field worker obtains written informed consent from the participant.

### Study procedures and visits

At the enrolment visit, study field workers administer a questionnaire to record sociodemographic, behavioural and clinical information in an online Research Electronic Data Capture (REDCap)^30^ software database. The study nurse examines the woman, according to the South African government standard of care.^31^ As an additional procedure, a study nurse with training in obstetric ultrasound performs an abdominal ultrasound to estimate the gestational age. If this is later than the eligibility criterion, the participant is excluded from any further study activity. A study nurse collects vaginal samples (figure 1) for on-site testing for *C. trachomatis* and *N. gonorrhoeae* using the Xpert CT/NG assay on the Gene Xpert platform (Cepheid, Sunnyvale, California, USA) and for further off-site laboratory testing (see ‘Specimen collection and analysis’).

If the test result for *C. trachomatis* or *N. gonorrhoeae* is positive, the woman receives immediate antibiotic treatment if still on-site or is contacted by telephone and asked to return to the clinic for treatment. Antibiotic treatments are first-line regimens according to South African guidelines: for *C. trachomatis*, 1 g oral azithromycin and for *N. gonorrhoeae*, 500 mg intramuscular ceftriaxone (250 mg until South African treatment guidelines for sexually transmitted infections changed in December 2022).^32^ Women with vaginal discharge syndrome but with negative Xpert test results for *C. trachomatis* and *N. gonorrhoeae* receive empirical treatment for trichomoniasis with metronidazole 400 mg twice a day for 7 days. The study nurse gives advice to women with *C. trachomatis* or *N. gonorrhoeae* on safe disclosure of her diagnosis to her partner(s) and gives her a notification slip(s) to request her partner(s) to attend a clinic for treatment.

A follow-up visit at 30–34 weeks (third trimester visit) is scheduled at which clinical and obstetric information, as well as the same vaginal specimens, is collected and treatment given, if indicated.

A postnatal visit is scheduled for 3–6 days after giving birth, according to the South African government standard.^31^ A study nurse collects information about the birth outcome and perinatal period through a questionnaire with the mother, a patient-held medical record of the baby (the Road to Health card) and/or the birth register from the public birth clinics within the study area. If the participant does not attend the postnatal visit, study staff telephone her to ask her to return to the clinic. If the participant is not able to return to the clinic, the study physician collects the information by telephone or from the birth register.

### Outcomes

The primary outcome is gestational age at birth, measured in days, based on the ultrasound assessment at the enrolment visit. Secondary outcomes are preterm birth (<37 completed weeks of gestation), low birth weight (birth weight <2500 g), miscarriage (dead fetus delivered before 28 completed weeks of pregnancy or with birth weight below 1000 g) and stillbirth (dead fetus delivered at or after 28 completed weeks of pregnancy or with birth weight above 1000 g).^33 34^ We chose gestational age at birth as the primary outcome because, while the cut-off of 37 weeks is the standard definition of preterm birth, dichotomisation of a continuous variable results in a loss of statistical power.^35^

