### Sample size calculation

The sample size has been calculated for objective 1, with a univariable comparison between the presence of a genital tract microorganism in the mother and gestational age at birth. Figure 2 shows that, for any vaginal or sexually transmitted microorganism, or vaginal microbiota type that has a prevalence of 10% or more among all enrolled women, about 500–600 patients provide adequate power (80%) to detect a 1-week difference (with SD 2) in mean gestational age between the two groups using Student’s t-test. Specifying an alpha of 0.83% allows for multiple hypothesis testing (six hypotheses, using a Bonferroni correction). We enrol around 600 women and aim to have complete follow-up and outcome data on at least 550 women.

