#### Objective 1: association between specified exposures and pregnancy outcomes

We will examine a primary set of microorganisms as exposures, detected at either enrolment or at the third trimester visit: *M. genitalium, M. hominis*, *U. urealyticum, U. parvum, T. vaginalis* and *Candida* spp are the microorganisms for which women did not receive diagnostic tests and treatment during study visits. We will use the mean and SD for the continuous outcome (gestational age) and absolute and relative frequencies for the binary outcomes (all secondary outcomes). Gestational age at birth for each exposure will be compared using Student’s t-test and a mean difference with 95% CIs (continuous outcome) and Fisher’s exact test and a risk difference with 95% CIs (binary outcomes).To control for confounding, multivariable regression models will be fitted to all outcomes with a set of prespecified potential confounders (age, educational level, alcohol consumption, HIV infection, prior preterm birth) for all organisms. For analyses of *M. genitalium*, *T. vaginalis* and *Candida* spp, we will also control for bacterial vaginosis (Nugent score 7–10). The other genital mycoplasmas can be identified from 16S rRNA amplicon sequencing in women with vaginal dysbiosis, so are sometimes considered part of bacterial vaginosis. For these organisms, we will conduct descriptive analyses, stratified by the presence of bacterial vaginosis. For continuous confounders, a linear relationship will be assumed by default but transformations (eg, log) or more flexible approaches (eg, splines or fractional polynomials) will be considered if there is evidence for non-linearity. For the continuous outcome, we will use linear mixed-effects regression models (including data from either visit and the participant as random effect) and report the result as mean difference with 95% CIs. For the binary outcome, we will use logistic mixed-effects regression and report the result as ORs with 95% CIs.Comparisons for associations with timing of detection, other microorganism exposures and birth outcomes will be considered secondary analyses. Associations between vaginal microbiota composition and pregnancy outcomes will be assessed. We will use compositional multivariable analysis methods to identify bacterial taxa that are differentially abundant between binary pregnancy outcome groups at the level of individual taxon relative abundances. We will use mixed-effects models (with the individual participant as the random effect and including data from both visits) to assess associations between continuous and binary pregnancy outcome and the following fixed effects derived from the vaginal microbiota data: alpha diversity, vaginal microbiota types and absolute abundances of predefined bacterial groups.^46^ These models will be adjusted for confounding as described in the previous paragraph.

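### Miscarriage and stillbirth are not mutually exclusive as defined: a fetal death whose gestational age and weight disagree meets both definitions

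*Protocol article*

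**What the plan says.** The Outcomes section of the protocol article lists four secondary outcomes: preterm birth, low birth weight, miscarriage and stillbirth. The last two are defined as follows:

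- For the earlier loss, with a weight limit of 1000 g: "miscarriage (dead fetus delivered before 28 completed weeks of pregnancy or with birth weight below".
- For the later loss, with the same limit approached from the other side: "stillbirth (dead fetus delivered at or after 28 completed weeks of pregnancy or with birth weight above".

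The same section bases gestational age on ultrasound: "The primary outcome is gestational age at birth, measured in days, based on the ultrasound assessment at the enrolment visit". Under Participants and under Study procedures and visits, an ultrasound estimate is part of confirming eligibility, so every woman who stays in the cohort has one.

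Under Objective 1, each secondary outcome is analysed separately as a binary variable, with "absolute and relative frequencies for the binary outcomes (all secondary outcomes"), Fisher's exact test, a risk difference and logistic models. Nowhere does the article say which criterion prevails when gestational age and weight disagree, or that a death may count under both outcomes.

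**The concern.** Miscarriage and stillbirth are ordinarily read as the two sides of one boundary, so that each fetal death falls on exactly one side. Here each side of the boundary can be reached by two routes, age or weight, and either route is enough. A death that is late by age but light by weight, or early by age but heavy by weight, therefore qualifies on both sides.

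Two analysts could follow the text in good faith and report different counts. One would apply the words literally and enter the discordant death twice. The other would assume that the outcomes exclude each other and add a tie-break of their own. These outcomes will have few events, so the choice could affect the reported risk differences and p-values, and it would be made after the data are seen unless a rule is fixed first.

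**Working it through.** **1. The two rules as logic.** For a dead fetus with gestational age GA (weeks) and birth weight W (grams), as the Outcomes section states them:

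- Miscarriage: GA < 28 or W < 1000
- Stillbirth: GA ≥ 28 or W > 1000

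| GA (weeks) | W (g) | Miscarriage | Stillbirth | Result |
|---|---|---|---|---|
| 27 | 900 | yes (age, weight) | no | one class |
| 27 | 1000 | yes (age) | no | one class |
| 27 | 1050 | yes (age) | yes (weight) | **both** |
| 30 | 900 | yes (weight) | yes (age) | **both** |
| 30 | 1000 | no | yes (age) | one class |
| 30 | 1050 | no | yes (age, weight) | one class |

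The clauses GA < 28 and GA ≥ 28 already cover every case, so no death is left unclassified. The overlap consists of exactly two groups: GA ≥ 28 with W < 1000, and GA < 28 with W > 1000.

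**2. Which count is affected.** Take classification by gestational age as the reference. Deaths at or after 28 weeks and under 1000 g are stillbirths; the literal rule also adds them to miscarriage. Deaths before 28 weeks and over 1000 g are miscarriages; the literal rule also adds them to stillbirth. Each type of discordant death inflates one count, not both.

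**3. How many.** The article gives no rate for either outcome and no proportion of discordant deaths. For illustration only, assume that 1–3% of 550 women (the follow-up target under Sample size calculation) have a stillbirth: 0.01 × 550 = 5.5 to 0.03 × 550 = 16.5 events. If 10–40% of these weigh under 1000 g (also an assumption), the overlap is 0.10 × 5.5 = 0.55 to 0.40 × 16.5 = 6.6 deaths. The lower end is less than one woman. The other type, before 28 weeks and over 1000 g, is not estimated here.

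**4. What one death can do.** Take 550 women with 10% exposed (the lowest prevalence for which the article claims adequate power): 0.10 × 550 = 55 exposed and 495 unexposed. The event counts are illustrative. Two-sided Fisher's exact test:

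| Events, exposed / unexposed | p | One death added | p |
|---|---|---|---|
| 3/55 vs 5/495 | 0.037 | 3/55 vs 6/495 | 0.051 |
| 2/55 vs 3/495 | 0.081 | 3/55 vs 3/495 | 0.015 |
| 2/55 vs 4/495 | 0.113 | 3/55 vs 4/495 | 0.025 |

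One added death can cross 0.05 in either direction. The direction of the association stays the same in all three rows.

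This is not typical of every table. With 6, 11 or 17 events in total, of which 0 to 7 are exposed (at most 6 when the total is 6), one extra unexposed event never crossed 0.05. One extra exposed event crossed it at a single starting split for each total (2 of 6, 3 of 11 and 4 of 17 exposed).

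**The case against.** The best defence is that nothing in the plan requires exclusive classes. Each secondary outcome is analysed alone, no composite or multinomial model is specified, and each can be tallied from its own definition. This stands as far as it goes: a reader might infer that the two outcomes cannot be counted at all, and that is too strong. They can be counted, but not as two distinct outcomes without either double counting or an unstated tie-break.

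A second defence is that the definitions are attributed to cited sources, which may use weight only when gestational age is unknown, and that a separate statistical analysis plan is promised. Both may be true, but the Outcomes section makes weight an alternative in every case, and that wording needs correcting wherever the rule is finally set.

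Four stronger readings are tempting and are not supported:

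- *A weight of exactly 1000 g falls through the gap.* It meets neither weight clause, but gestational age assigns it. It would matter only if gestational age were unknown.
- *Both event counts are inflated by the same deaths.* Against a gestational-age rule, each type of discordant death adds to one count only.
- *The overlap is large enough to reverse a comparison.* The rates behind any such figure are assumptions, and the calculation shows only that a borderline p-value can cross 0.05.
- *The overlap changes which exposure visit is relevant.* The primary exposures are those detected at either visit, and timing of detection is a secondary analysis. A death at 28 or 29 weeks precedes the visit at 30–34 weeks just as an earlier loss does.

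**Conclusion.** The point holds as a defect in two of the four secondary outcome definitions. They are exhaustive but not mutually exclusive, and a literal reading enters every discordant death under both. This follows from the wording alone and needs no assumption.

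The size of the effect cannot be derived from the article. The number of discordant deaths is probably small and may be zero or one; the illustrative range of 0.55 to 6.6 for one type rests wholly on assumed rates. A single such death can matter for a borderline Fisher's exact test, as the examples with 55 exposed and 495 unexposed women show, but most tables would not change their conclusion.

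Gestational age at birth, as the primary outcome, and the sample size calculation do not depend on these definitions. This is a correction worth making before analysis, not a threat to the study's main result.

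**What to change.** State one precedence rule in the Outcomes section, or in the statistical analysis plan before analysis, so that each fetal death falls in exactly one class. Ultrasound-based gestational age is already collected for every enrolled woman, so it is the natural first criterion: delivery before 28 completed weeks is a miscarriage, and at or after 28 completed weeks a stillbirth. Use birth weight, below 1000 g against 1000 g or more, only when gestational age at delivery cannot be established. The second weight category then includes 1000 g itself, which matters once weight is the sole criterion.

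If the authors prefer another order of precedence, stating it beforehand would equally remove the overlap. The cost is one sentence and counts that may differ slightly from a literal reading; no new data are needed.
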